**7. Data Management and Monitoring**

- Data will be stored in a secure electronic database with regular backups.
- An independent data monitoring committee will oversee trial safety and protocol adherence.
- Regular audits will ensure data accuracy and compliance with ethical standards.

**8. Justification for Ethical Approval**

This study addresses a critical gap in comparative data on implant surgical techniques, with potential to improve clinical outcomes and patient satisfaction. The trial poses minimal additional risk beyond standard implant procedures, as all techniques are established in clinical practice. Ethical safeguards include:

- Rigorous informed consent process.
- Minimization of risks through standardized protocols and experienced surgeons.
- Robust data protection measures.
- Immediate reporting and management of adverse events.
- Adherence to international ethical standards.

The study’s findings will contribute to evidence-based dentistry, potentially improving treatment protocols for partially edentulous patients globally.

**9. Funding**

Funded by the Deanship of Scientific Research at King Khalid University (Grant Number RGP1/3/46).

**10. Declarations**

- **Ethics Compliance**: The study will comply with the Declaration of Helsinki.
- **Competing Interests**: The investigators declare no competing interests.
- **Data Availability**: All relevant data will be included in the published manuscript, ensuring transparency.

**11. Supporting Documents**

- Informed consent form (in Arabic and English).
- Participant information sheet.
- Case report forms.
- Draft questionnaire for patient satisfaction.
- CBCT imaging protocol.

**1. Purpose**

The CBCT imaging protocol aims to:

- Provide accurate preoperative assessment of bone anatomy and volume for implant planning.
- Verify postoperative implant placement accuracy by comparing planned and actual implant positions.
- Ensure consistent imaging parameters to minimize variability and radiation exposure while maintaining diagnostic quality.

**2. Scope**

This protocol applies to all 90 participants enrolled in the RCT, covering preoperative and postoperative CBCT scans for the freehand (FHIS), pilot-drilled (PDIS), and fully guided (FGIS) implant surgery groups.

**3. Equipment**

- **CBCT Scanner**: Carestream CS 9600 or equivalent, calibrated to manufacturer specifications.
- **Software**: Carestream 3D Imaging Software (or compatible software) for image acquisition, processing, and analysis.
- **Calibration**: The CBCT unit will be calibrated weekly to ensure consistent image quality and radiation output, following manufacturer guidelines and ALARA (As Low As Reasonably Achievable) principles.

**4. Imaging Parameters**

To ensure reproducibility and diagnostic accuracy, the following standardized parameters will be used:

- **Field of View (FOV)**:
  - Small FOV (5x5 cm or 8x8 cm) for single-tooth or small-segment edentulous areas.
  - Medium FOV (10x10 cm) for larger edentulous spans or multiple implants, ensuring inclusion of adjacent teeth and anatomical landmarks (e.g., inferior alveolar nerve, maxillary sinus).
- **Voxel Size**: 0.2 mm for high-resolution imaging to assess fine bone details and implant positioning.
- **kVp**: 90 kVp (range: 80–100 kVp, adjusted based on patient size to optimize image quality).
- **mA**: 5–10 mA, adjusted to minimize radiation dose while ensuring diagnostic clarity.
- **Exposure Time**: 10–15 seconds, depending on the FOV and patient cooperation.
- **Rotation**: 360° for comprehensive 3D reconstruction.
- **Image Format**: DICOM (Digital Imaging and Communications in Medicine) for compatibility with implant planning software.

**5. Preoperative CBCT Procedure**

**Purpose**: To assess bone volume, density, and anatomical structures for implant planning. **Timing**: Performed within 2 weeks before surgery.

**Procedure**:

1. **Patient Preparation**:
   - Remove all metallic objects (e.g., jewelry, removable dentures) to avoid artifacts.
   - Provide a lead apron with a thyroid collar to minimize radiation exposure to non-target areas.
   - Position the patient upright in the CBCT scanner, with the head stabilized using a chin rest and head straps to prevent movement.
   - Instruct the patient to remain still and avoid swallowing during the scan.
2. **Scan Acquisition**:
   - Center the FOV on the edentulous area, including adjacent teeth and critical anatomical structures (e.g., inferior alveolar nerve, mental foramen, maxillary sinus).
   - Use a scout view to confirm correct positioning before the full scan.
   - Perform the scan using the parameters specified above.
3. **Image Processing**:
   - Reconstruct images in axial, coronal, and sagittal planes.
   - Export DICOM files to implant planning software (e.g., NobelClinician or Blue Sky Plan) for virtual implant placement and surgical guide fabrication (for FGIS group).
4. **Quality Check**:
   - A radiologist will review images for clarity, absence of artifacts, and inclusion of all relevant anatomical structures.
   - Repeat scans if motion artifacts or positioning errors are detected (anticipated in <5% of cases).

**6. Postoperative CBCT Procedure**

**Purpose**: To evaluate implant placement accuracy by comparing actual implant positions to preoperative plans. **Timing**: Performed within 1 week post-surgery.

**Procedure**:

1. **Patient Preparation**: Same as preoperative procedure.
2. **Scan Acquisition**:
   - Use the same FOV and parameters as the preoperative scan to ensure comparability.
   - Focus on the implant site, including surrounding bone and adjacent teeth.
3. **Image Analysis**:
   - Measure deviations in implant position (mesiodistal, buccolingual, and angular) and depth (mm) using superimposition of preoperative and postoperative images.
   - Assess osseointegration indicators (e.g., bone-implant contact) and detect complications (e.g., bone perforation).
   - Analysis will be performed by a blinded radiologist to minimize bias.

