**2. Study Objectives**

**Primary Objective**: To compare the efficacy of freehand, pilot-drilled, and fully guided implant surgery in partially edentulous patients with respect to surgical outcomes (duration, complications), postoperative recovery (pain, swelling), implant stability, osseointegration, and patient satisfaction.

**Secondary Objectives**: To evaluate long-term implant success rates and summarize the advantages and limitations of each technique to optimize clinical protocols.

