**Key Outcomes**:

- Surgical duration (minutes).
- Implant placement accuracy (via postoperative CBCT).
- Postoperative complications (within 30 days).
- Early implant failure rates (within 6 months).
- Patient satisfaction (via validated 10-point questionnaire at 6 months).
- Implant stability (via Resonance Frequency Analysis at 3, 6, and 12 months).
- Pain and swelling (via Visual Analogue Scale on Days 1 and 3).

**Study Duration**: January 6, 2025 (recruitment start) to August 3, 2025 (final follow-up).
**Sample Size**: 90 patients (30 per group), calculated for 80% power and alpha of 0.05, assuming a medium effect size (Cohen’s d = 0.5) for implant placement accuracy, with a 10% dropout rate.

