**10. Ethical Considerations**

- **Informed Consent**: Patients will be informed about the purpose, benefits, and low radiation risks of CBCT imaging as part of the study consent process.
- **Minimizing Exposure**: Only necessary scans (one preoperative, one postoperative) will be performed.
- **Confidentiality**: All imaging data will be anonymized and stored securely, in compliance with the Declaration of Helsinki and institutional ethics guidelines (ECM#2024-3195).

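### Osseointegration is in the primary objective, but its only assigned reading is bone contact on a CBCT taken within a week of surgery, which reflects fit at placement rather than healing

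*Protocol*

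**What the plan says.** Protocol section 2 (Study Objectives) lists, within the primary objective, "postoperative recovery (pain, swelling), implant stability, osseointegration, and patient satisfaction", after surgical duration and complications. Osseointegration is thus an item of its own, distinct from stability.

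The Key Outcomes list in section 3 has no osseointegration entry. The two entries that bear on the implant after the early postoperative period are "Implant stability (via Resonance Frequency Analysis at 3, 6, and 12 months") and "Early implant failure rates (within 6 months").

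The CBCT imaging protocol, section 6, gives the timing of the postoperative scan as "Performed within 1 week post-surgery" and its purpose as "To evaluate implant placement accuracy by comparing actual implant positions to preoperative plans". Under Image Analysis in the same section, the radiologist is nevertheless also told to "Assess osseointegration indicators (e.g., bone-implant contact) and detect complications (e.g., bone perforation").

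Section 10 of the CBCT protocol rules out later imaging: "Only necessary scans (one preoperative, one postoperative) will be performed".

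**The concern.** A construct named in the primary objective is paired with a reading at a time that cannot capture it. In the first week, contact between bone and implant on CBCT reflects how closely the prepared site fits the implant. The three arms differ in how the site is prepared, so this contact could differ by arm for purely mechanical reasons. Followed as written, the protocol would record that difference under the name of osseointegration, and it could then be reported against the primary objective as a difference in healing. Blinding the radiologist does not help, because the problem lies in what is measured and not in who reads it. An analysis plan could not repair it either, since no analysis turns a first-week image into evidence of later integration.

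**Working it through.** There is no stated figure to reproduce. The check compares the sections with each other and does simple date arithmetic.

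**1. Share of the primary objective affected.** Section 2 names duration, complications, pain, swelling, implant stability, osseointegration and patient satisfaction: 7 components, of which 1 is affected.

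**2. Where osseointegration is assessed.**

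| Place in the protocol | What it gives for osseointegration |
|---|---|
| Section 2, primary objective | Named as a component |
| Section 3, Key Outcomes | No entry |
| Section 6, Data Collection | No entry; RFA, complications and satisfaction are listed |
| CBCT protocol section 1, Purpose | Not mentioned |
| CBCT protocol section 6, purpose of the postoperative scan | Not mentioned; placement accuracy only |
| CBCT protocol section 6, Image Analysis | Bone-implant contact on the postoperative scan |

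The last row is the only assigned assessment.

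**3. Timing.** The scan falls on day 0 to 7. The first RFA is at 3 months, about day 91. The gap from the latest permitted scan is 91 − 7 = 84 days, or 12 weeks.

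**4. Could another scan supply the reading?** Section 10 of the CBCT protocol allows one postoperative scan. The repeat-scan provision in the preoperative procedure covers motion artifacts and positioning errors, not follow-up. No later CBCT is planned.

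**5. Do the later measures fit the study dates?** This bears on the remedy. Recruitment runs from 6 January to 3 February 2025 and final follow-up is 3 August 2025 (sections 3 and 4).

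- From the start of recruitment to final follow-up: 209 days, about 6.9 months.
- From the close of recruitment to final follow-up: 181 days, exactly 6 calendar months.
- 3-month RFA: a patient operated on by 3 May 2025 reaches it by 3 August, so there is ample room.
- 6-month RFA and 6-month failure status: reached only by patients operated on by 3 February 2025. The preoperative CBCT may precede surgery by up to 2 weeks, so a patient enrolled near the close could be operated on after that date and miss 6 months.
- 12-month RFA: even for surgery on 6 January 2025 it would fall on 6 January 2026, outside the window for every patient.

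The 3-month RFA is therefore available within the stated dates, the 6-month measures are at the edge, and the 12-month RFA cannot be relied on.

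**The case against.** The strongest reply is that the trial already collects relevant data. RFA at 3 and 6 months and failure by 6 months both bear on whether an implant has integrated. A reader might infer from the early scan that this part of the objective cannot be answered, or that osseointegration is unmeasurable in this trial. The documents do not support that: indirect evidence is planned. What is missing is any statement linking it to osseointegration. The protocol labels RFA as stability and lists stability as a separate component. This part of the objection stands and limits the point.

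A reader might also infer that the protocol itself treats integration as taking months. It does not say so. Its 3- and 6-month time points are consistent with that view, but the healing time is general subject knowledge.

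A further reply is that the Image Analysis line is only an instruction to the radiologist, with no stated comparison between arms, and that operational definitions may sit in case report forms or an analysis plan not shown here. It is true that misreporting is a risk and not a certainty. But if the line means only initial contact, then its label is wrong and the component of the primary objective has no assigned measure at all. The text needs changing on either reading.

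Finally, the consequence is limited: the sample size is based on placement accuracy, which the 1-week scan serves properly. That also stands.

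**Conclusion.** The point holds in a limited form. The primary objective includes osseointegration, and the only assessment assigned to it is a bone-contact reading on the single postoperative CBCT, at most 7 days after surgery and about 12 weeks before the first RFA. An arm difference in that reading could be mislabelled as a difference in osseointegration. The defect touches 1 of 7 components of the primary objective, in all 90 patients. It does not touch placement accuracy, the sample size, allocation or safety.

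The conclusion rests on one assumption from outside the documents: that contact seen in the first week reflects placement and not healing. It does not extend to saying that the component cannot be addressed, because RFA and early failure could inform it indirectly once the protocol says so. The correction should be made, because the text as it stands assigns the wrong meaning to a planned reading and the change is cheap.

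**What to change.** 1. In the CBCT imaging protocol, section 6, Image Analysis, delete the reference to osseointegration indicators. Keep position, angulation, depth and perforation.
2. Then do one of two things:
   - state in section 2 and in Key Outcomes that osseointegration is inferred indirectly from the planned RFA (3 months, and 6 months where the study window allows) and early implant failure, without counting it as a separate outcome; or
   - remove the term from the primary objective.

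   Defining it as an implant in place without failure at 6 months and listing that as a new outcome is not advised, because this is essentially the complement of early failure, which is already listed.
3. Reconcile the 6-month time point with the 3 August 2025 end of follow-up, since any patient operated on after 3 February 2025 would not reach it. The 12-month RFA needs the same attention.

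Steps 1 and 2 are wording changes and need no extra scan, visit or radiation. If step 3 is resolved by extending follow-up, that has its own cost in study duration. The price of the correction is that the trial claims one fewer directly measured component.

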**7. Radiation Safety**

- **ALARA Principle**: Radiation doses will be minimized by using the smallest FOV necessary and optimizing kVp/mA settings.
- **Dose Estimation**: Typical effective dose for small/medium FOV scans is 50–150 µSv, well below the threshold for significant risk.
- **Patient Information**: Patients will be informed about the low radiation risk and necessity of CBCT for treatment planning and evaluation.
- **Staff Training**: Only certified radiographers will operate the CBCT scanner, following radiation safety protocols.

**8. Data Management**

- **Storage**: DICOM files will be stored in a secure, password-protected database with unique patient identifiers to ensure confidentiality.
- **Access**: Only authorized study personnel (radiologists, investigators) will access imaging data.
- **Analysis**: Images will be analyzed using validated software to quantify implant placement accuracy and bone characteristics.
- **Retention**: Imaging data will be retained for 5 years post-study, per institutional guidelines, and then securely deleted.

**9. Quality Assurance**

- **Calibration**: Weekly calibration of the CBCT scanner to maintain image quality and radiation accuracy.
- **Standardization**: All scans will follow the same protocol to ensure consistency across participants.
- **Blinding**: Radiologists analyzing postoperative images will be blinded to the surgical technique to reduce bias.
- **Audit**: An independent reviewer will audit 10% of scans to verify protocol adherence and image quality.

**10. Ethical Considerations**

- **Informed Consent**: Patients will be informed about the purpose, benefits, and low radiation risks of CBCT imaging as part of the study consent process.
- **Minimizing Exposure**: Only necessary scans (one preoperative, one postoperative) will be performed.
- **Confidentiality**: All imaging data will be anonymized and stored securely, in compliance with the Declaration of Helsinki and institutional ethics guidelines (ECM#2024-3195).

**11. Personnel**

- **Radiologist**: Responsible for image acquisition, quality control, and analysis.
- **Radiographer**: Trained to operate the CBCT scanner and ensure patient positioning.
- **Investigators**: Oversee integration of CBCT data into surgical planning and outcome assessment.

**12. Documentation**

- CBCT scan parameters and findings will be recorded in standardized case report forms.
- A log of all scans, including date, time, and any adverse events (e.g., need for repeat scans), will be maintained.
